### Objectives

The aim of this study is to evaluate the impact of an mHealth clinical pharmacist and HC intervention in African-Americans and Latinos with poorly controlled type 2 diabetes. We hypothesize that the mHealth intervention will improve HbA_1c_, blood pressure, and low-density lipoprotein (LDL) as well as medication and lifestyle behavior adherence compared with usual care. In addition, the crossover design will test the hypothesis that improvements in outcomes resulting from the intervention in year 1 will be maintained during the maintenance period (usual care) in year 2.

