**Figure 1 figure1:**
[figure not shown]
Randomized crossover study design.

The primary outcome is the change in HbA_1c_ level. Secondary outcomes include changes in blood pressure and LDL cholesterol levels. Using a 1:1 ratio, we will randomize 220 patients to either (1) a mHealth intervention delivered by a clinical pharmacist and HC for 1 year, followed by usual care for 1 year, or (2) usual care for 1 year, followed by the mHealth intervention for 1 year. Both groups will crossover at the end of year 1, such that those receiving the mHealth intervention during the first year will receive usual care during the second year (to evaluate potential maintenance of outcome improvement). Similarly, those with usual care in year 1 will crossover to receive the intervention in year 2 (to ensure that all subjects are able to receive the intervention). Of note, we do not consider HbA_1c_ levels collected at the end of year 1 when crossover occurs. The treatment received by patients (intervention or usual care) will change at the end of year 1, independent of HbA_1c_ levels.

Separate randomization schedules generated in REDCap will be used for each of the 4 main clinical sites with stratification for ethnic group (African-American and Latino) and gender to balance the proportion of participants across randomized conditions. All study procedures have been approved by the University of Illinois at Chicago Institutional Review Board (IRB 2016-0380).

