#### Sample Size Justification

The sample size calculation is powered to detect the primary outcome, which is the change in HbA_1c_. Reviews of published studies suggest that successful education programs lower A_1c_ levels by 0.4% to 1.7% [3,103]. On the basis of our previous experience with the patient population, we estimated a mean baseline HbA_1c_ level of 10% with a SD of 1.8 and an effect size of 0.56 for aim 1. The cross-time correlation was estimated to be 0.30, with a compound symmetry structure. We adjusted for clustering and assumed an intraclass correlation coefficient of 0.01, with 5 clusters. This yielded a design effect of 1.34. Two-sided alpha of .05 and 80% power were assumed. Allowing for a 20% dropout rate, 220 patients were required [104].

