Univariate comparisons between the 2 study groups for outcomes and covariates at baseline will be conducted using chi-square tests for categorical variables, Kruskal-Wallis tests for ordinal variables, and *t* tests for continuous variables. All tests will be two-sided. Nonnormal continuous data will be transformed before the analysis. To provide a comprehensive analysis of our primary hypothesis, we will extend the usual analysis of crossover designs [111] by including a longitudinal trend component in the first year. Thus, we can examine the time course (0, 6, and 12 months) as linear or quadratic over the first 3 measurements. This will allow us to investigate whether changes are made early and at what rate they continue throughout the rest of the period. This analysis permits a comparison of the trends between the 2 conditions. In addition, we will regard subjects as a random effect and will use Gaussian mixed model estimation. We can then substitute treatment by period interactions for the carry-over effects, and the model can be reduced in a recommended sequence (first omit carry-over, then omit treatment, and finally omit period) [111]. We will also explore patterned covariance structures such as compound symmetry and autoregression along with incorporating time-constant and time-varying covariates, such as health literacy or diabetes distress.

The primary analysis of all physiological outcomes jointly in the repeated measures design will be conducted using a general linear model framework. Repeated measures multivariate analysis of variance will be used to explore the simultaneous impact of the treatment on multiple correlated dependent variables, including the use of Roy-Bargmann stepdown *F* tests and discriminant function analysis as post hoc tests to identify subsets of outcome measures affected [112]. Multivariate analysis of variance (MANOVA) secondary analyses will explore the impact of inhomogeneous baseline variables on the results. Group by time-trend interaction contrasts will be used to explore different group trajectories of change. The potential consequences of medication intensification (eg, initiation of insulin) will be explored by evaluating changes in BMI and quality of life.

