Exploratory subgroup analyses will follow a heterogeneity in treatment effects framework [113,114]. We will determine which subjects in the intervention group had the greatest improvement in outcomes, based on multiple prespecified patient characteristics, including race (African-American or Latino), depression, comorbidities, baseline behaviors, health literacy, continuity of care, and social support. These analyses will also consider additional comparisons between subjects above and below the median levels of videoconferencing and text messaging activity. Statistical tests will be implemented as interactions within the full data set.

If the intervention results in improved HbA_1c_ more than that in the usual care, we will examine whether changes in self-efficacy, health beliefs, or social support serve as mediators for improved outcomes. In addition, we will explore diabetes-related behaviors as well as medication treatment intensification as mediators using MPlus [115-118]. To further identify the relative contributions of videoconferencing and/or text messaging, we will conduct meditational modeling with videoconferencing time, number of text messages, and HC contact time as mediating variables. This may describe any dose-response relationship between mHealth utilization and outcomes. We will compute bias-corrected bootstrap standard errors using MPlus. This offers accurate confidence intervals for mediation coefficients [119]. Due to anticipated relationships between HC activity level and mHealth delivery, we plan to inspect correlations between mediators and incorporate any significant findings in model development. This analysis will demonstrate whether the intervention effects are sensitive to mediators. Finally, given the sample size, observed (rather than latent) variables will be used in the mediation models. To enhance the power of mediation modeling, we adopt an α=.10 type I error criterion to improve the chances of finding promising mediators for future studies.

We expect a limited amount of decline in physiologic outcomes with the transition back to usual care. We will test the hypothesis that improvements in HbA_1c_ (primary outcome), blood pressure, and LDL cholesterol (secondary outcomes) will be maintained during the maintenance period. The analyses will be conducted in a manner similar to our primary hypothesis and will evaluate changes in the initial intervention group 1 year after intervention completion.

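### Maintenance in year 2 is a no-loss hypothesis, but it is given a difference-type analysis with no margin and no stated reference time point, so a non-significant decline would not show it

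*Protocol article*

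**What the plan says.** The Objectives section makes durability a hypothesis to be tested: "improvements in outcomes resulting from the intervention in year 1 will be maintained during the maintenance period (usual care) in year 2". The last paragraph of Data Management and Analysis repeats it for HbA1c, blood pressure and LDL, and adds an expectation without a number: "We expect a limited amount of decline in physiologic outcomes with the transition back to usual care".

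The same paragraph fixes two features of the analysis:

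- Method: "The analyses will be conducted in a manner similar to our primary hypothesis".
- Group: it "will evaluate changes in the initial intervention group 1 year after intervention completion".

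The primary approach, set out earlier in that section, is a mixed-model crossover analysis with time trends, group-by-time contrasts and a multivariate analysis of variance. On testing in general the section says "All tests will be two-sided". No margin, retained fraction or equivalence criterion is given for maintenance.

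On the other arm, the Study Design section says that "those with usual care in year 1 will crossover to receive the intervention in year 2". The Sample Size Justification covers the change in HbA1c for aim 1 ("Two-sided alpha of .05 and 80% power were assumed"). It does not size the maintenance question.

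**The concern.** A difference test can supply evidence that something changed. Failing to find a change is not evidence that nothing changed, and the failure becomes more likely as the sample shrinks or the data get noisier. A hypothesis of no important loss needs the opposite logic: the data must exclude a loss larger than some stated amount. The plan expects a limited decline, so it already needs a threshold that separates limited decline from failure to maintain, and it gives none.

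The starting point of the change is also open. Measured from month 12, the contrast addresses loss. Measured from baseline, it addresses whether some improvement is still present. These are different questions with opposite error directions.

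Finally, nobody is on usual care without previous intervention in year 2. Entry required HbA1c of at least 8.0%, so the 24-month level in the initial intervention group mixes retained effect with regression to the mean and drift over time. At stake is one of the trial's two stated hypotheses. The year-1 comparison between arms is unaffected.

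**Working it through.** **The plan's own figures.** The plan gives no figure for maintenance. Its design effect reproduces: 220 × 0.8 = 176 completers, and 1 + (176/5 − 1) × 0.01 = 1.342. The total of 220 could not be reproduced from the stated inputs, because the article gives neither the formula nor the unit of the 0.56 effect size. Nothing below depends on that total beyond the number of completers.

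**Inputs**

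- SD 1.8, cross-time correlation 0.30 with compound symmetry, 20% dropout (Sample Size Justification).
- Completers in the initial intervention group: 110 × 0.8 = 88. The Results section reports 109 actually randomized.
- Size of benefit: 0.42 points (health-coach-augmented arm of the team's earlier trial, Background). The plan's 0.56 is read either as points or as SD units (0.56 × 1.8 = 1.01 points).
- Assumption: complete loss means a mean rise from 12 to 24 months equal to the benefit, with no other drift.

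**Precision of the 12-to-24-month change**

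- SD of change = 1.8 × √(2 × (1 − 0.30)) = 2.13.
- SE = 2.13/√88 = 0.227.
- 95% half-width = 1.96 × 0.227 = 0.445 points.

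An observed rise of 0.42 points, the whole benefit of the earlier trial, would therefore be non-significant.

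**Chance of a non-significant result.** For a true loss d this is Φ(1.96 − d/SE) − Φ(−1.96 − d/SE).

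| Benefit (points) | All lost | Half lost |
|---|---|---|
| 0.42 | 54% | 85% |
| 0.56 | 31% | 77% |
| 1.01 | 0.7% | 40% |

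**Sensitivity, complete loss**

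| Setting | 0.42 | 0.56 | 1.01 |
|---|---|---|---|
| All 109 patients, correlation 0.30 | 46% | 22% | 0.1% |
| 88 completers, design effect 1.34 applied (effective n 65.7) | 64% | 43% | 3% |
| 88 completers, assumed correlation 0.5 | 41% | 17% | below 0.1% |
| 88 completers, assumed correlation 0.7 | 19% | 3.5% | below 0.1% |

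**Power of a margin rule.** If nothing is truly lost, the chance that the upper 95% limit falls below margin m is Φ(m/SE − 1.96).

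- m = 0.5: 0.5/0.227 − 1.96 = 0.24, so about 60%.
- m = 0.28 (half of 0.56): 23%.
- m = 0.21 (half of 0.42): 15%.

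For 80% power with half the benefit as margin, the arm would need 808, 455 and 141 completers for benefits of 0.42, 0.56 and 1.01 points, before any design effect. The one-half is an illustration; the plan does not give it.

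**The case against.** **No decision rule is stated.** A reader might infer that the trial will declare maintenance whenever the decline is non-significant. The article does not say so, and a success criterion for a later hypothesis could sit in an analysis plan that is not shown. This stands as a limit on the claim. What remains is that the article itself pairs a no-loss hypothesis with a difference approach.

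**The contrast could start at baseline.** The primary outcome is the change in HbA1c, so the maintenance analysis could mean baseline to 24 months. Noise would then make success harder, and the argument about non-significance would not apply. The wording allows this, though the reference to maintenance during year 2 fits a 12-to-24-month contrast better. The baseline reading would still leave regression to the mean unresolved. The ambiguity is part of the point.

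**It need not be an isolated single-arm test.** The Objectives section says "the crossover design will test the hypothesis that improvements in outcomes" are maintained, and the primary approach is a two-arm model with carry-over or treatment-by-period terms. This is fair: the article does not say that only a paired test in one arm will be used. But a joint model does not supply a year-2 usual-care comparator that the design lacks.

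**A benefit must first be shown.** With a 0.45-point benefit (the earlier trial's pharmacist-only figure) that is entirely lost, simulation with the inputs above gives year-1 significance in 29% (change score) to 41% (baseline-adjusted). The later loss is non-significant in about 32% of those cases. Both happen together in 9–13% of trials, and in under 1% for a 1.01-point benefit. So the percentages in the working are conditional on the true loss. They are not the overall probability of a wrong durability claim.

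**Conclusion.** The point holds as a mismatch between hypothesis and method, with an undefined success criterion and an unstated reference time. It rests on reading the contrast as 12 to 24 months and the method as a two-sided difference analysis. Both are close inferences, not explicit text.

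Its size depends on the benefit. For 0.42 to 0.56 points, non-significance is a poor guide: complete loss would be missed 54% to 31% of the time under the plan's SD and correlation. A reader might infer that total disappearance of any benefit could pass unnoticed. The figures do not support that for a benefit of 1.01 points, where complete loss would be missed under 1% of the time, although loss of half would still be missed 40% of the time.

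Nor is the absent year-2 comparator an oversight. The Study Design section explains that the crossover lets every participant receive the intervention. It can be acknowledged but not repaired in the analysis. This is a change that should be made, and it does not threaten the primary result.

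**What to change.** In Data Management and Analysis, or in the analysis plan before the 24-month data are analysed:

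1. Name the 12-to-24-month change in the initial intervention group as the maintenance contrast. Report it with its 95% confidence interval, alongside the change from baseline to 24 months.
2. Claim maintenance of HbA1c only if the upper 95% limit of the rise is below a fixed numeric margin, justified and set in advance. A margin defined as a share of the observed year-1 benefit is not a fixed number: it carries its own sampling error and sets a within-arm rise against a between-arm estimate.
3. Otherwise report the estimate and interval, and say that maintenance will not be inferred from a non-significant decline.
4. State that year 2 has no concurrent usual-care arm, so regression to the mean and drift cannot be separated from retained effect.

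The cost is wording only, with no new patients or visits. The downside is that maintenance becomes harder to claim: power is about 60% for a 0.5-point margin with no true loss, and only about 15–23% for a margin of half of a 0.42–0.56-point benefit. If the benefit is that small, the trial should expect to report an estimate and interval without a maintenance claim.

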## Results

The study was initiated in July 2016, and enrollment began in March 2017. Figure 2 shows the Consolidated Standards of Reporting Trials diagram for recruitment.

**Figure 2 figure2:**
[figure not shown]
Consolidated Standards of Reporting Trials flow diagram. mHealth: mobile health.

As shown in Table 2, 221 patients have been enrolled, exceeding our goal of 220 patients. A total of 112 patients have been randomized to usual care for their first year, and 109 patients have been randomized to the mHealth intervention.

The retention rate is currently 90% for subjects completing the first year of the study. We anticipate that data collection will be completed in November 2021. Following data analyses, the manuscript will be developed with primary results by May 2022 for peer-reviewed publication.

**Table 2 table2:** Demographic characteristics of study population.

Characteristic		Usual care (n=112)	Intervention (n=109)
Age (years), mean (SD)		54.5 (9.6)	56.0 (9.3)
Diabetes duration (years), mean (SD)		12.3 (7.9)	13.1 (7.7)
**Ethnicity, n (%)**			
	Latino or Hispanic	36 (32.1)	37 (33.9)
	African-American	76 (67.9)	72 (66.1)
**Gender, n (%)**			
	Male	35 (31.2)	32 (29.4)
	Female	77 (68.7)	77 (70.6)
**Language preference, n (%)**			
	English	97 (86.6)	87 (79.8)
	Spanish	15 (13.4)	22 (20.2)
**Income (US** $**), n (%)**			
	Less than 10,000	38 (33.9)	36 (33.0)
	10,000-19,999	19 (17.0)	26 (23.8)
	20,000-29,999	12 (10.7)	16 (14.7)
	30,000-39,999	7 (6.2)	10 (9.2)
	40,000-49,999	12 (10.7)	0 (0)
	50,000-59,999	6 (5.4)	8 (7.3)
	60,000-69,999	2 (1.8)	3 (2.8)
	70,000 or more	14 (12.5)	8 (7.3)
	Refused to answer	2 (1.8)	2 (1.8)
**Education, n (%)**			
	Less than high school	26 (23.6)	29 (26.6)
	High school diploma or equivalent	22 (19.6)	33 (30.3)
	Some college, 2-year certificate, or associates degree	41 (36.6)	26 (23.8)
	College graduate (4 year)	11 (9.8)	13 (11.9)
	Some graduate school	3 (2.7)	3 (2.8)
	Graduate degree	8 (7.1)	5 (4.6)
	Other	1 (0.9)	0 (0)
**Health status, n (%)**			
	Excellent	2 (1.8)	0 (0)
	Very good	4 (3.6)	5 (4.6)
	Good	42 (37.5)	38 (34.9)
	Fair	47 (42.0)	58 (53.2)
	Poor	17 (15.2)	8 (7.3)
**Insurance, n (%)**			
	None	5 (4.5)	8 (7.3)
	Public	69 (61.6)	70 (64.2)
	Private	36 (32.1)	30 (27.5)
	Other	2 (1.8)	1 (0.9)

## Discussion

This study assesses the effectiveness of a novel mHealth approach for improving diabetes self-management in an underserved, minority population with type 2 diabetes. The study will provide further evidence of the use of mHealth in both clinical and community environments, with tools to support clinical pharmacists and HCs in their patient-oriented activities. If effective, this intervention can be considered for implementation in low-resource settings where pharmacist services are not readily available, and HCs can extend the reach of providers targeting patients with limited access to care.

### Strengths and Limitations

The study is innovative in several ways. The proposed study will be the first randomized controlled trial to evaluate an mHealth intervention to improve diabetes management in low-income African-Americans and Latinos with type 2 diabetes delivered through HCs. This study builds upon prior work and is responsive to patient feedback in offering remotely delivered videoconferencing with clinical pharmacists who collaborate with HCs to improve diabetes outcomes [56]. Pharmacist videoconferencing overcomes the transportation barriers commonly experienced by individuals with limited income. We currently use scalable, inexpensive mHealth tools (VSee and *mytapp*) to promote adoption in low-resource clinical organizations, including Federally Qualified Health Centers.

A number of limitations and challenges have been identified. First, there is the potential for contamination across groups, as randomization was not clustered. Intervention and usual care patients may share the same provider and clinical site. In addition, we recruited patients from a single urban health care system, which may limit generalizability. Additional studies in practice networks would require the availability of clinical pharmacists and HCs. Finally, our intervention integrates multiple components: clinical pharmacists, HCs, videoconferencing, and text messaging, so we are unable to determine the impact of each component individually.

In conclusion, despite the widespread use of mobile devices, little is known about the effectiveness of the technology in improving health care delivery or outcomes. Although systematic reviews show the preliminary value of text messaging, patient education apps, and videoconferencing in chronic disease management, most studies have been small in size, underpowered, and low in quality and include motivated, nonminority subjects. This study will provide the evidence needed on the impact of mHealth diabetes adherence support delivered to low-income minority patients with uncontrolled type 2 diabetes.

## Appendix

Multimedia Appendix 1 Peer-review report by National Institute of Diabetes and Digestive and Kidney Diseases (NIDDK).

## Abbreviations

DSME/S: diabetes self-management education and support
EMR: electronic medical record
HbA1c: hemoglobin A1c
HC: health coach
HIPAA: Health Information Portability and Accountability Act
LDL: low-density lipoprotein
MANOVA: multivariate analysis of variance
mHealth: mobile health
PCP: primary care provider
RA: research assistant
UI Health: University of Illinois Hospital and Health Sciences System
